### Research design and procedure

This research will use a mixed methods design. First, a two-armed randomized-controlled trial will be employed to evaluate the clinical effectiveness of the brief MBI on personal recovery outcomes, with study participants randomized into a brief MBI group or a waiting list control group according to a computer-generated randomization list. The brief MBI will incorporate the basic theory and research of foundation mindfulness-based cognitive therapy (MBCT; 30) and is adapted from the treatment manual of MBCT for BD [21]. As usual, the programme will be conducted in group format [21, 30]. Furthermore, information and data gained from pilot quantitative and qualitative studies will be incorporated into the design and modification of the brief MBI intervention.

The brief MBI intervention will consist of four weekly sessions of 120 min each. The themes and contents of the brief MBI sessions are summarized in Table 2. The brief MBI will be conducted in groups of about 8 to 10 participants and led by therapists qualified in mindfulness teaching. Daily home practice will be encouraged and recorded for the participants in the brief MBI group. The waiting list control group will continue with routine care in hospital-based or community-based settings but will be offered the brief MBI intervention after 6 months (the final study follow-up assessment). While participants will be aware of the group to which they have been allocated, outcome assessors and data analysts will be kept blind to the allocation.

**Table 2 Tab2:** Themes and contents of the brief MBI

Themes	Intention of interventions	Major mindfulness practice
1. Welcome in the moment	Introduction of mindfulness; experiential learning and practice of mindfulness; start off a mindfulness journey in daily life	➢ Movement exercise and brief sitting meditation practice ➢ Raisin exercises ➢ Yoga-Body scan ➢ Breathing space introduction ➢ Home practice
2. Responding with depression	Deepen mindfulness experience; experiential learning thoughts ➔ emotions relationship; emotion-focused meditation (depression); learning ways to respond with depression	➢ Body scan ➢ Mindful sitting with breath, sounds and thoughts ➢ Automatic negative thoughts scenarios (thoughts ➔ emotions) ➢ Emotion-focused meditation – depression ➢ Breathing space ➢ Home practice

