### Sampling

On the basis of the data from the pilot study results and according to the G*Power programme [45], and in order to achieve a statistical power of 0.8 with a medium effect size (f = 0.35) and a significance level of 0.05 in repeated measures, a multivariate analysis of variance under the proposed two-group, three-time-point design and a total sample size of 82 will be needed. Furthermore, for the path model analysis of the underlying mechanism with two latent variables and seven observed variables, a sample size of 138 is needed, according to an online calculator [46]. In addition, and as recommended by Kline [47], the minimum sample size to parameters ratio should be 10:1 in a path model. As there will be 10 potential parameters in the proposed model, the minimum sample size needed is 100. Thus, we will plan for a total of 138 participants. Assuming an attrition rate of about 10%, a final sample size of 154 (i.e., 77 per condition) will be enrolled into the study and randomized.

The inclusion criteria are as follows: (1) a diagnosis of Bipolar I or II disorder; (2) in a state of full remission for more than 2 months [48]; (3) no active suicidal ideation or self-harm behaviours; (4) on regular medication; and (5) aged 18 years old or above. People with a comorbid diagnosis of schizophrenia, schizoaffective disorder, substance misuse, organic brain syndrome, or intellectual disability will be excluded. A Structured Clinical Interview for DSM-IV Disorders (SCID; only the mood disorders sections) [49] will be administered by trained clinicians to confirm the diagnosis and remission status of the participants. Observation of mental state and any potential for self-harm behaviours will be closely monitored throughout the intervention and assessment processes. When necessary, participants will be advised to consult a professional. After completing the project, participants will be given cash coupons as incentives. Suitable participants will be recruited from various hospital-based and community-based psychiatric rehabilitation settings across Hong Kong. With an agreed partnership with a local non-governmental organization (NGO) and a collaborated hospital, initial permission has been sought for recruiting participants from these settings.

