### Data analysis

The data will be analyzed using SPSS, version 24.0. The associations among different variables will be investigated using Pearson’s correlation analysis. To test Hypothesis 1, a factorial ANOVA with repeated measures will be conducted. Hierarchical linear modelling (HLM) will be employed to test the individual growth model by studying repeatedly measured data. This integrated random-coefficients approach is usually conceptualized as a two-level model. Level 1, or the within-subject model, is the model for repeated measures with time-varying variables nested within individuals, whereas level 2, or the between-subject model, is the model for time-invariant variables between groups of individuals. SPSS mixed will be used in performing the HLM. In order to reduce the possible effects of multicollinearity, grand mean centring of different plausible predictors will be done before further data analysis. The fit of the models will be assessed and compared using appropriate fit statistics, including likelihood ratio tests and Akaike information criterion correction [50].

To test Hypotheses 2 and 3, the macro PROCESS SPSS and the bootstrapping approach [51] will be used to assess the moderated mediation effects in the path model. Each predictor will be mean centred to form the interaction terms. The effects of covariates such as age or gender will be adjusted accordingly. The PROCESS macro is based on ordinary least squares regression. In all analyses, the significance level will be set to *p* < 0.05.

To test Hypothesis 4, the contents of the focus group interview will be audiotaped and transcribed by a team of independent raters. Thematic analysis will be conducted with the help of the software NVivo (version 10.1.3) for storing and managing the data. The coding and analysis will use interpretative phenomenological analysis (IPA [52];). The IPA will allow a bottom-up approach to determine the themes. Throughout the analysis, the codes will be identified from frequently used words or ideas from the transcripts. Codes will then be categorized into larger recurrent themes for further analysis. The combined analysis of the Photovoice pieces and corresponding narratives will use the iconographic and thematic analyses approaches [53]. The research team will meet to discuss the significance of each theme and triangulate the results with the quantitative findings.

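### The brief MBI is given in therapist-led groups in one arm only, but every planned model treats participants as independent, so the 0.05 level is not held if outcomes correlate within groups

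*Protocol article*

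**What the plan says.** All references are to the protocol article.

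- **Randomization** (Research design and procedure) is of individuals: "with study participants randomized into a brief MBI group or a waiting list control group according to a computer-generated randomization list".
- **Delivery** (same section) is grouped in the active arm: "The brief MBI will be conducted in groups of about 8 to 10 participants and led by therapists qualified in mindfulness teaching". The comparison arm is not grouped: "The waiting list control group will continue with routine care in hospital-based or community-based settings". Controls are offered the programme only after the final assessment.
- **Hypothesis 1** (Data analysis): "To test Hypothesis 1, a factorial ANOVA with repeated measures will be conducted". A hierarchical model for individual growth, run in SPSS MIXED, follows: "This integrated random-coefficients approach is usually conceptualized as a two-level model". Level 1 "is the model for repeated measures with time-varying variables nested within individuals". The other level is the person: "whereas level 2, or the between-subject model, is the model for time-invariant variables between groups of individuals". The groups mentioned there belong to the between-subject level; no random effect for the treatment group is described.
- **Hypotheses 2 and 3** (Data analysis) use the PROCESS macro, which the section says rests on ordinary least squares.
- **Sample size** (Sampling): 82 for the repeated-measures analysis and 138 for the path model. "Thus, we will plan for a total of 138 participants"; allowing for 10% attrition gives 154, or 77 per arm. No ICC or design effect appears.

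**The concern.** This is a partially nested trial. With 77 people in groups of 8 to 10, the MBI arm has about 8 to 10 groups (77/10 = 7.7; 77/8 = 9.6), each sharing a therapist, a set of sessions and fellow participants. The article's own background section presents the group format as helpful to participants in itself, so some correlation of outcomes within a group is plausible.

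A model whose highest unit is the person counts 77 independent MBI participants. If the group correlation is positive, the variance of the MBI mean is understated. The BRQ arm contrast then gets an interval that is too narrow and a p-value that is too small, so the error favours declaring the MBI effective. Any model with treatment arm as the predictor of a mediator has the same weakness.

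This goes beyond detail left to an analysis plan. The article names the levels of the model and the least-squares method, and a plan that handled the groups would have to depart from both.

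**Working it through.** **Inputs from the article.** Group size m = 8 to 10 (9 used below), MBI arm only; alpha 0.05; power 0.80; f = 0.35; two groups, three time points; N = 82 for Hypothesis 1; 138 for the path model; 10% attrition; 154 randomized, 1:1.

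**Assumed.** ICC among members of an MBI group: 0.01 to 0.10.

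**Step 1: reproduce the stated sample sizes.** For the group-by-time test in a repeated-measures MANOVA, take noncentrality λ = f² × N with 2 and N − 3 degrees of freedom.

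- N = 82: λ = 0.1225 × 82 = 10.0, power 0.801.
- N = 80: power 0.791.
- 138/0.9 = 153.3, rounded up to an even 154.

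The 82 is what independent participants require, and the step from 138 to 154 is attrition alone. Neither contains an allowance for clustering.

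**Step 2: effect of ignoring the groups.** With equal arms and clustering in one of them:

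- design effect in the MBI arm: DE = 1 + (m − 1) × ICC
- true variance of the arm difference relative to the naive one: V = (1 + DE)/2
- actual two-sided type I error = 2 × [1 − Φ(1.96/√V)]

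| ICC (assumed), m = 9 | DE | V | Naive SE too small by | Type I error |
|---|---|---|---|---|
| 0 | 1.00 | 1.00 | 0% | 5.0% |
| 0.01 | 1.08 | 1.04 | 1.9% | 5.5% |
| 0.02 | 1.16 | 1.08 | 3.8% | 5.9% |
| 0.05 | 1.40 | 1.20 | 8.7% | 7.4% |
| 0.10 | 1.80 | 1.40 | 15.5% | 9.8% |

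Worked line for ICC 0.05: DE = 1 + 8 × 0.05 = 1.40; V = 2.40/2 = 1.20; 1.96/√1.20 = 1.79; two-sided tail 7.4%. Over m = 8 to 10 the range is 5.4% to 5.5% at ICC 0.01, 7.1% to 7.7% at 0.05 and 9.2% to 10.4% at 0.10.

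**Step 3: check by simulation.** 20,000 trials per setting; 69 per arm after attrition; eight MBI groups of 8 or 9; a shared group effect at T2 and T3; assumed between-visit correlation 0.6. The naive group-by-time test rejected a true null in 4.7% of trials at ICC 0, then 5.4%, 6.1%, 7.4% and 10.4% at ICC 0.01, 0.02, 0.05 and 0.10. This agrees with the formula.

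**Step 4: consequence for sample size.** Multiply the stated N by V, for m = 9 and ICC 0.01 / 0.05 / 0.10:

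- Hypothesis 1: 82 becomes 86 / 99 / 115. All lie below 138. Power at 138 is about 0.92 at ICC 0.05 and 0.88 at ICC 0.10.
- Path model: 138 becomes 144 / 166 / 194 if the same multiplier is applied. This is only indicative, because the 138 comes from an online path-model calculator and the simple design effect need not carry over to it.

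**Step 5: do the remedies work with about eight groups?** In simulation (69 per arm, eight groups, ICC 0 to 0.10), comparing MBI group means with individual controls, using Satterthwaite degrees of freedom, kept type I error at about 5% to 6%. A percentile bootstrap that resampled whole MBI groups gave about 7% to 9%, and was above 5% even at ICC 0.

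**The case against.** **The ICC is unknown and may be small.** Therapists must be qualified and experienced, they share a two-day training, and sessions are recorded and rated by independent assessors, all of which limits differences between groups. At ICC 0.01 to 0.02 the error rate is 5.5% to 5.9%, which few would worry about. This stands. A reader might infer that the type I error certainly exceeds 5%, but the article does not support that without an ICC.

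**Larger inflation can be derived.** A reader might take the BRQ test-retest correlation of 0.866 as the pre-post correlation and, holding the post-score ICC at 0.05, arrive at nearly 15% for change scores. But 0.866 is a 4-week reliability figure, and the trial also has a six-month follow-up. The change score would have variance 2 × (1 − 0.866) = 0.268, so the calculation implies a change-score ICC of 0.05/(0.268 + 0.05) = 0.16 or more, outside the range assumed here. That figure should not be used.

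**The sample size looks unadjusted, hence too small.** For Hypothesis 1 this does not follow: step 4 shows ample room at 138 on the article's own f. Nor does the sample size cause the excess type I error; the model does, and more participants in groups of the same size would not cure it.

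**Not every mediation path is equally exposed.** The Measurements section and Table 1 label mindfulness (FFMQ), a person-level score, as the independent variable. If FFMQ rather than arm is the predictor, the inflation depends on clustering in both FFMQ and the outcome and will generally be smaller. No path was computed here, so no size is claimed for mediation.

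**The two-level sentence is generic, and SPSS MIXED is already planned.** True, but the ANOVA and PROCESS statements are specific and share the gap. That MIXED is in the plan makes the correction easier; it does not supply it.

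**Conclusion.** The point holds in conditional form. The article specifies group delivery in one arm and names three analyses, none of which represents the groups. If the within-group ICC is positive, the BRQ arm contrast has standard errors that are too small: by about 2% at ICC 0.01, 9% at 0.05 and 16% at 0.10. The actual error rates are then about 5.5%, 7.4% and 9.8%. These figures rest on about 9 per group, equal arms and ICC values that are assumed because the article gives none. At ICC 0 there is no inflation. Hypothesis 1 power is adequate on the stated f = 0.35. Mediation models with arm as predictor share the weakness, to an extent not quantified here.

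**What to change.** 1. Record MBI group and therapist for every participant in the intervention arm. Without the identifiers, later correction may be impossible.
2. Make the Hypothesis 1 analysis a partially nested mixed model in SPSS MIXED: the planned repeated-measures structure plus a random MBI-group effect in the intervention arm only, each control being its own unit, with Satterthwaite-type small-sample degrees of freedom.
3. For mediation, fit the treatment-to-mediator and outcome models with the same random effect, at least as a sensitivity analysis beside PROCESS. Do not rely on a cluster bootstrap over about eight groups (step 5).
4. State in the Sampling section that 82 and 138 assume independent participants, and give the assumed ICC with its effect: for Hypothesis 1, about 99 needed at ICC 0.05.

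The cost is one or two identifier variables, one random-effect statement and somewhat wider intervals. No increase in recruitment is needed for Hypothesis 1 at the stated f.

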## Methods/design

### Aims of the research project

Here, we propose a research programme that addresses all of the aforementioned knowledge gaps, including research that will enable us to understand the psychological mechanisms underlying recovery [7]. Specifically, the aims of the research project are as follows:
To examine the effectiveness of a brief MBI for enhancing personal recovery in a sample of individuals with BD relative to a waiting list control condition.To evaluate the mediating roles of emotion awareness, emotion regulation, and illness acceptance as mechanisms underlying the beneficial effects of the brief MBI.To investigate the moderating role of BD stage on the beneficial effects of the brief MBI.To better understand the participants’ lived experience of mindfulness in relation to the personal recovery process.

On the basis of the conceptual model depicted in Fig. 1, we will address these aims by testing the following specific hypotheses:
The brief MBI will be more effective, with a higher effect size, than the waiting list control on measure of the primary outcome of personal recovery.The beneficial effects of the brief MBI on measure of personal recovery will be mediated by treatment-related increases in emotion awareness, emotion regulation, and illness acceptance.The hypothesized mediation effects will be moderated by BD stage: that is, individuals with BD who report having a lower number of previous BD episodes will evidence stronger mediation effects for treatment-related changes in emotion awareness and emotion regulation, whereas individuals with BD who report having a higher number of previous BD episodes will evidence stronger mediation effects regarding illness acceptance.The qualitative analysis will increase our understanding of the effects and mechanisms of the brief MBI interventions.

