### Measurements

The psychometric attributes of all the measurement tools used in this project, such as reliability and validity, are psychometrically sound. For those assessments without a Chinese version, translation and cultural adaptation have been made with reference to the guidelines for the translation and adaptation of psychometric scales [36]. Outcome assessment will take place at baseline (T1), after intervention (T2), and at a six-month follow-up (T3). All participants will be assessed in terms of the following:

Primary outcome:

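### The mediation model for Hypotheses 2 and 3 does not specify adjustment for the baseline mediator and BRQ scores, or which visit supplies mediator and outcome

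*Protocol article*

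**What the plan says.** For the second and third hypotheses, the Data analysis section of the protocol article states that "the macro PROCESS SPSS and the bootstrapping approach [51] will be used to assess the moderated mediation effects in the path model". It adds that "The PROCESS macro is based on ordinary least squares regression", that predictors are mean-centred to form interaction terms, and, on adjustment, "The effects of covariates such as age or gender will be adjusted accordingly".

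Hypothesis 2 (Aims of the research project) is that the benefit "will be mediated by treatment-related increases in emotion awareness, emotion regulation, and illness acceptance". Hypothesis 3 likewise refers to "stronger mediation effects for treatment-related changes in emotion awareness and emotion regulation".

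The Measurements section fixes three visits for all scales: "Outcome assessment will take place at baseline (T1), after intervention (T2), and at a six-month follow-up (T3"). The article therefore has T1 values of every mediator and of the BRQ. The mediation paragraph does not say whether they enter the model, or which visit supplies the mediator and which the outcome. The repeated-measures ANOVA and the hierarchical model, which use all three visits, are described for Hypothesis 1.

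**The concern.** A PROCESS regression uses one record per person, so three visits do not enter it unless someone decides how. Two decisions determine what is estimated: whether baseline levels are held fixed, and whether the mediator is measured before the outcome.

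Randomisation protects the path from treatment to mediator. It does not protect the path from mediator to outcome. Someone with little self-stigma at T1 will probably have a high recovery score at T1, T2 and T3 whatever the treatment does. Unless T1 levels are in the model, that pre-existing association enters the mediator-to-outcome coefficient and hence the indirect effect. The trial could then report a mechanism that does not exist. A mediator and outcome taken at the same visit also cannot show that the mediator changed first.

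Leaving T1 out also makes the treatment-to-mediator path noisier than it needs to be.

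**Working it through.** **Inputs from the article**
- Sampling: 138 needed for the path model and 10% attrition. 138/0.90 = 153.3, rounded up to an even 154, or 77 per arm; this reproduces. With 138 analysed there are 69 per arm. No power is stated for the mediation tests.
- Table 1 (pilot, 10 per arm): post-score d of 0.38 (DERS), 0.29 (ISMI), 0.26 (MDIS) and 0.22 (ERS). For DERS, (97.8 − 90.6)/√[(19.89² + 18.07²)/2] = 7.2/19.00 = 0.379, which reproduces.
- Measurements: retest correlations of 0.84 over 2 weeks (DERS), 0.75 over 1 week (MDIS) and 0.866 over 4 weeks (BRQ).
- Level 0.05, taken as two-sided.

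**Assumptions (not in the article)**
- Correlation of T1 with follow-up, ρ: 0.5 to 0.84.
- Baseline mediator-outcome correlation, c: 0.3 to 0.5.
- All scores standardised, no direct effect of treatment, and T1 scores the only source of confounding.

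**Step 1: mediator-to-outcome path when the true effect is zero**

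Model: M2 = ρ·M1 + d·T + error and Y3 = ρ·Y1 + error, with corr(M1, Y1) = c. Within arm, cov(M2, Y3) = ρ²c and var(M2) = 1, so a regression without T1 scores estimates ρ²c instead of 0. With change scores, cov = (1 − ρ)²c and var = 2(1 − ρ), so the estimate is (1 − ρ)c/2.

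| ρ | c | Bias, no T1 | Bias, change scores | Bias, T1 M and T1 BRQ included |
|---|---|---|---|---|
| 0.5 | 0.3 | 0.075 | 0.075 | 0 |
| 0.5 | 0.5 | 0.125 | 0.125 | 0 |
| 0.7 | 0.3 | 0.147 | 0.045 | 0 |
| 0.7 | 0.5 | 0.245 | 0.075 | 0 |
| 0.84 | 0.3 | 0.212 | 0.024 | 0 |
| 0.84 | 0.5 | 0.353 | 0.040 | 0 |

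Simulation at N = 138 agrees with these values. False rejection of this path ran from 14% (ρ = 0.5, c = 0.3) to 99% (ρ = 0.84, c = 0.5) without T1 scores, and was about 5% throughout with them. With change scores at c = 0.5 it was about 30%, 14% and 7% at ρ = 0.5, 0.7 and 0.84.

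A mediation claim also needs the treatment-to-mediator path. With joint significance of the two paths standing in for the bootstrap, a false indirect effect appeared without T1 scores in 3% to 25% of runs at d = 0.22 and 9% to 62% at d = 0.38. With T1 scores it appeared in at most 5%.

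**Step 2: power of the treatment-to-mediator path**

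Two-sample t test, 69 per arm, effect d/√(1 − ρ²).

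| True d | Unadjusted | ρ = 0.5 | ρ = 0.6 | ρ = 0.7 | ρ = 0.84 |
|---|---|---|---|---|---|
| 0.38 | 60% | 73% | 79% | 87% | 98% |
| 0.22 | 25% | 32% | 36% | 44% | 66% |

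**Step 3: can the pilot d be carried into step 2?**

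The DERS d is a post-score difference, and the arms already differed by 99.8 − 97.2 = 2.6 points at T1. The adjusted difference is 7.2 − ρ(19.00/20.23)·2.6, where 20.23 is the pooled T1 standard deviation.
- ρ = 0.6: 5.73 points, d = 0.30, power about 59%.
- ρ = 0.84: 5.15 points, d = 0.27, power about 83%.

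The 79% and 98% therefore belong to a true d of 0.38, not to the DERS pilot result after baseline adjustment. For ISMI and MDIS the T1 imbalance runs the other way.

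**The case against.** A reader might infer that the plan adjusts for age and gender alone and ignores both the T1 scores and the order of the visits. The text does not support that. The covariates are given as examples, no sentence excludes T1 scores, and no visit is assigned, so a T2-then-T3 model is not ruled out. The sample-size text counts seven observed variables and the Fig. 1 note lists six scales, which leaves little room for separate T1 scores. Age and gender are not in that count either, so this is no more than a hint.

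The hypotheses also speak of increases and changes, which suggests change scores. At ρ = 0.84 these would recover nearly all the power at d = 0.38: the effect becomes 0.38/√(2 × 0.16) = 0.67, with power near 98%. They would also remove most of the bias. At ρ = 0.5, however, they gain nothing on either path, since √(2 × 0.5) = 1 and the two bias formulas coincide. That value is plausible over six months.

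It is also fair to say that an article may leave a full covariate list to an analysis plan. But this paragraph is not silent: it fixes macro, estimator, centring and example covariates, and omits the covariates that matter most for this estimate.

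Finally, a large loss of power cannot be asserted outright. The quoted retest values cover 1 to 4 weeks, and the pilot effects come from 10 people per arm. That criticism stands.

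**Conclusion.** The point holds as an underspecified model with a clearly better alternative that uses data already collected; it is not a stated decision to discard baseline. If the model were run without T1 scores, the mediator-to-outcome path would be biased by ρ²c, about 0.07 to 0.35 over the assumed ranges, with false rejection of 14% to 99% against about 5%. Including T1 mediator and T1 BRQ removes this bias in the simulated setting. In practice it removes only the confounding those scores carry.

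The power gain is secondary and conditional: for a true d of 0.38, from 60% to between 73% and 98% as ρ goes from 0.5 to 0.84. The bias argument does not rest on it.

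Baseline adjustment is the firm part. Making T2-to-T3 the main model is preferable for temporal order but more open to debate. The test of Hypothesis 1 is unaffected; the interpretation of Hypotheses 2 and 3 depends on this being settled before the data are analysed.

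**What to change.** In the Data analysis text for Hypotheses 2 and 3:

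- Include the T1 mediator score and the T1 BRQ score as covariates in both the mediator equation and the outcome equation. List any other covariates, such as age and gender, as a closed set.
- State the visit of each variable, preferably mediator at T2 and BRQ at T3, with a model using both at T2 as a sensitivity analysis.
- State that the mediator-to-outcome path remains non-randomised, so the indirect effect rests on there being no further confounding after T1 adjustment.

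The cost is a change of wording and a few more regression terms. No new data are needed. The lagged model uses only people with a T3 BRQ score, which the same-visit T2 model partly offsets.

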➢ Personal experiences of BD recovery: This will be assessed using the Bipolar Recovery Questionnaire (BRQ; 37). This 36-item questionnaire measures an individual’s experiences of recovery, such as personal understanding of self, sense of personal agency, or identifying recovery as a dynamic process. Total score is calculated by summing individual scores across all items. Evidence supports the internal consistency of the total score (*α* = .875) and good test-retest reliability over 4 weeks (*r* = .866) [37]. A higher total score indicates better personal recovery.Mediators:➢ Emotion awareness and emotion regulation: These will be assessed using the Chinese version of the Difficulties in Emotion Regulation Scale (DERS [38];) and the Emotion Reactivity Scale (ERS [39];). The DERS is a 36-item questionnaire that measures adults’ difficulties in emotion regulation. Evidence supports the scale’s internal consistency (*α* = .9) and good test-retest reliability over 2 weeks (*r* = .84) [38]. A higher total score suggests greater problems with emotional regulation. The ERS is a 21-item self-report measure of emotion sensitivity, intensity and persistence. Evidence demonstrates the good consistency (*α* = .94) of the scale [39]. A higher total score indicates greater emotional reactivity.➢ Illness acceptance: This will be assessed by the Internalized Stigma of Mental Illness Scale (ISMI [40];) and the Mood Disorders Insight Scale (MDIS [41];). The ISMI is a 9-item short form that measures self-stigma. Evidence supports the good consistency of the scale (*α* = .86) [40]. A higher total score reflects higher levels of reported internalized stigma. The MDIS is an 8-item scale that measures insight of mood disorders. Evidence supports the scale’s satisfactory test-retest reliability over 1 week (*r* = .75). Validity testing of the scale was based mainly on clinician ratings (r = 0.49) [41]. A higher total score indicates greater insight.Moderator:➢ BD stage will be operationalized as the number of previous BD episodes [6, 25]. Consistent with previous prospective studies on BD stage [13, 42], the number of previous episodes will be categorized as less than 5, 5 to 10, and more than 10.Independent variable:➢ Mindfulness: This will be assessed by the Chinese version of the Five Facet Mindfulness Questionnaire (FFMQ [43];). The FFMQ is a 39-item questionnaire which consists of five subscales: Observing, Describing, Acting with Awareness, Non-judging of Inner Experience, and Non-reactivity to Inner Experience. The five factors form a total mindfulness score which reflects a global measure of mindfulness. Evidence supports the scale’s good consistency (*α* = .83) and test-retest reliability over 2 weeks (*r* = .88) [43]. A higher total score indicates greater levels of mindfulness.

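### Adjusting for age as a covariate does not keep age differences in response out of the BD-stage interaction, so attributing moderation to stage would not be supported

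*Protocol article*

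**What the plan says.** The aims include "To investigate the moderating role of BD stage on the beneficial effects of the brief MBI", and Hypothesis 3 makes this specific: "The hypothesized mediation effects will be moderated by BD stage". It predicts stronger mediation through emotion awareness and regulation in people with fewer episodes, and through illness acceptance in people with more.

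Under Measurements, "BD stage will be operationalized as the number of previous BD episodes", and "the number of previous episodes will be categorized as less than 5, 5 to 10, and more than 10". Under Sampling, participants are "aged 18 years old or above", with no upper limit.

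Under Data analysis, Hypotheses 2 and 3 are tested with PROCESS and bootstrapping. "Each predictor will be mean centred to form the interaction terms". The next sentence deals with age: "The effects of covariates such as age or gender will be adjusted accordingly". Then: "The PROCESS macro is based on ordinary least squares regression". No term combining age with arm, or age with a mediator, is mentioned.

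**The concern.** Randomisation balances the arms; it does not separate stage from age. Within a person the episode count can only grow, and adults of any age are eligible, so a positive correlation between stage and age is plausible.

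Hypothesis 3 is decided by an interaction. Age as a covariate takes out age differences in the level of the mediator or outcome. If people of different ages respond differently to the MBI, that difference is an age-by-arm effect, and a main effect of age leaves it in place. A correlated stage-by-arm term then carries part of it. The stated adjustment therefore looks like control for age but does not control it in the term that matters.

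At stake is the interpretation. The Background and Discussion present stage as a basis for matching the intervention to illness progression. If the difference came from age, that reading would be misplaced.

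**Working it through.** **Inputs from the protocol.** Analysable N = 138; attrition about 10%; two equal arms; significance level 0.05 (taken as two-sided); three stage categories; pilot effects on the mediators d = 0.22 to 0.38. The enrolled sample reproduces: 138 / 0.9 = 153.3, rounded up to 154.

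**Inputs assumed, because the protocol gives neither.** Age-stage correlation ρ from 0.3 to 0.7. Age slope g, the change in arm effect per SD of age in residual SDs of the mediator, mainly 0.1 to 0.3.

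**Direct calculation.** Code arm as ±0.5, standardise stage and age, and let the arm effect be d + g × age with no stage effect at fixed age. Since E(age | stage) = ρ × stage, the arm effect given stage is d + g × ρ × stage. The stage-by-arm coefficient therefore centres on g × ρ, not on zero. Its standard error is about 2/√138 = 0.170.

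Example, g = 0.3 and ρ = 0.5: 0.15 / 0.170 = 0.88. The chance of exceeding ±1.96 is P(Z > 1.08) + P(Z < −2.84) = 0.140 + 0.002, about 14%. For g = 0.1 and ρ = 0.3: 0.03 / 0.170 = 0.18, giving about 5%.

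**Simulation.** N = 138, average arm effect 0.38 SD, three equal-sized stage groups scored linearly, no stage effect at fixed age, age as a covariate only. ρ is the correlation before stage is cut into groups. The last row uses a continuous stage score and an average arm effect of 0.3 SD.

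| Age slope g | ρ = 0.3 | ρ = 0.5 | ρ = 0.7 |
|---|---|---|---|
| 0.1 | 5.7% | 5.5% | 6.4% |
| 0.2 | 5.9% | 7.6% | 11.5% |
| 0.3 (three groups) | 7.5% | 12.4% | 19.1% |
| 0.3 (continuous stage) | 7.5% | 14.2% | 22.8% |

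With g = 0 or ρ = 0 the rate stays near 5%, so the excess comes from the stated mechanism. With age-by-arm added it returns to about 5% throughout.

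**Index of moderated mediation.** A percentile bootstrap with the arm-to-mediator path moderated, at g = 0.4, gave 11.1%, 21.5% and 31.8% at ρ = 0.3, 0.5 and 0.7 with age as covariate only, and 6.6%, 6.3% and 7.6% with age-by-arm added. The mechanism therefore carries over to the kind of test planned. The slope of 0.4 is large, as the next step shows.

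**What the slopes mean.** With an average effect of 0.38 SD, g = 0.2 gives 0.38 − 0.20 = 0.18 at 1 SD below mean age and 0.58 at 1 SD above. For g = 0.3 the figures are 0.08 and 0.68. For g = 0.4 they are −0.02 and 0.78, so the benefit has vanished 1 SD below mean age.

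**Cost of the added term.** The stage interval widens by √(1/(1 − ρ²)): 1.15 at ρ = 0.5 and 1.40 at ρ = 0.7, where ρ is the correlation of age with the stage score as entered. For a true stage interaction of 0.4 SD per SD of stage, simulated power in the three-group set-up falls from 62% to 58% (ρ = 0.3), 63% to 54% (0.5) and 64% to 43% (0.7).

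**The case against.** The strongest reply is that the plan may be asking a descriptive question. The Discussion wants to know for which patients the MBI works best. In the calculation above the arm effect really does differ across stage groups, so a significant term is not false as a description. This stands, and it limits the point to attribution.

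Second, the wording on covariates does not expressly exclude an age interaction, and a condensed article may leave such detail elsewhere. That is fair. But age is named apart from the predictors that form the interactions, so covariate-only is the plain reading of what is stated.

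Third, the size rests on assumptions. A reader might infer that the stage test has a false-positive rate of 30 to 50%. The documents do not support that: they give no age-episode correlation and no sign that response varies with age, and rates that high require a slope above the average treatment effect together with a strong correlation.

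Fourth, Hypothesis 3 predicts a crossed, directional pattern. The rates above are two-sided and concern one path. The chance of wrongly supporting the whole pattern was not computed, and a uniform age effect would contradict half of it.

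Fifth, other correlates of episode count, such as illness duration, raise the same question. Adding age alone would not establish that stage is the cause. Age is singled out because the protocol itself names it for adjustment.

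**Conclusion.** The point holds as a limit on interpretation. The stated age adjustment does not separate stage from age in the term that decides Hypothesis 3, so a stage difference could be reported as a description but not credited to illness stage over age.

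The excess of significant stage terms is small for modest age slopes (about 5 to 12% in all, against a nominal 5%) and moderate at 0.3 SD (about 8 to 23%). Both ranges depend on assumed correlations of 0.3 to 0.7 and on response varying with age at all; if either is absent, there is no excess.

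A reader might go further and call the planned test invalid, or any stage finding false. The documents do not support that. The primary comparison under Hypothesis 1 and the stated sample sizes are unaffected.

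**What to change.** Keep the planned PROCESS model as the main test of Hypothesis 3. Pre-specify one sensitivity model per mediator, with age as a second moderator on the same path or paths as stage. Report the stage estimate and its interval from both models side by side. If the estimate shrinks materially or reverses, describe the moderation as not separable from age; what counts as material should be fixed beforehand.

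The cost is one extra model per mediator and no new data. The stage term in that model is less precise: its interval is about 15% wider at a correlation of 0.5 and about 40% wider at 0.7. Loss of significance there should therefore not by itself overturn the main result. The sensitivity model qualifies the interpretation; it is not a veto.
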